## Abstract

**Introduction:**

Despite advances in acute treatment, stroke remains the first cause of acquired disability. Today, there is no effective pharmacological therapy to improve recovery beyond the acute phase. Preclinical studies suggest that inhibition of the C-C chemokine Receptor 5 (CCR5) may promote recovery by enhancing plasticity in the peri-infarct cortex. However, the role of CCR5 to improve outcome after ischaemic stroke in humans is unknown.

**Methods and analysis:**

MAraviroc for STrokE Recovery is a phase II, single-centre, randomised, double-blind, placebo-controlled trial. The aim is to assess the efficacy and safety of the CCR5 antagonist Maraviroc for improving motor recovery of the upper limb after ischaemic stroke. 80 ischaemic stroke patients with moderate but incomplete upper extremity motor impairment will be enrolled within 7 days of onset. Participants will be randomised (1:1) to receive either oral maraviroc (300 mg two times per day) or placebo for 90 days in addition to standard rehabilitation therapy. The primary outcome is upper limb motor function assessed using the Fugl-Meyer Assessment for the Upper Extremity at day 90. Secondary outcomes include motor learning skills and plasticity in the peri-infarct region assessed using MRI connectivity and spectroscopy at 90 days.

**Ethics and dissemination:**

The study protocol has been reviewed and approved by the Geneva Competent Ethics Committee (Commission Cantonale d’Éthique, CEC; Reference Number: CCER 2024-02359) and Swissmedic (Swiss Agency for Therapeutic Products). Written informed consent will be obtained from all participants. Study results will be disseminated through peer-reviewed publications and scientific conferences.

**Trial registration number:**

2024-02359; NCT07080567.

STRENGTHS AND LIMITATIONS OF THIS STUDYFirst study to initiate treatment in the acute phase of stroke (≤7 days after onset) to evaluate the efficacy of maraviroc to improve motor function.Use of standardised clinical outcomes combined with MRI-based measures to determine the clinical and neural correlates of drug effect.This study is limited to evaluating the effect of maraviroc on upper extremity function.The study assesses only a single treatment regimen.

## Introduction and rationale

 Persistent neurological deficits are frequent after stroke. Today, there are no effective pharmacologic therapies to improve stroke recovery beyond the acute phase.^1^ Pharmacological interventions offer advantages: they are not reliant on patient motivation, easy to administer and require fewer medical resources.

Maraviroc is a small-molecule inhibitor of the CCR5 receptor (C-C chemokine Receptor 5).^2^ This treatment has been developed for HIV therapy following the discovery that CCR5 is an essential co-receptor for the entry of the virus into host cells.^3^ This strategy was further supported by the observation that individuals homozygous for the CCR5-Δ32 mutation, which prevents surface expression of the receptor, were naturally resistant to HIV infection.^3^

CCR5 inhibition has emerged as a potential strategy to enhance plasticity after stroke in rodent models. Nevertheless, the timing of CCR5 inhibition appears critical, as transient poststroke pharmacological inhibition improves plasticity but constitutional genetic deletion may worsen outcomes.^4^

In rodents, CCR5 inhibition using maraviroc was associated with increased dendritic spine density in peri-infarct cortex and increased projecting axons between the peri-infarct cortex to the homologous contralateral cortex.^5^ These plastic changes correlated with behavioural performance, even beyond the acute phase.^5^ However, findings from genetic models complicate the interpretation of the role of CCR5 in recovery. Following middle cerebral artery occlusion, infarct size was markedly increased in constitutionally CCR5-deficient mice.^6^ Ubiquitous lack of CCR5 expression in mice appears deleterious for stroke recovery, on the contrary to the benefit of pharmacological inhibition by maraviroc.

In humans,^2 7^ no data have yet confirmed the potential of maraviroc after stroke. A loss-of-function CCR5 mutation was associated with a better recovery in ischaemic stroke patients.^5^ Pharmacological inhibition of the CCR5 receptor appears as a promising strategy to improve recovery after stroke.

Here, we present MAraviroc for STrokE Recovery (MASTER) trial protocol, designed to investigate the efficacy and mechanisms of action of maraviroc to improve motor recovery after ischaemic stroke.

## Methods

### Hypothesis

Maraviroc improves motor recovery after ischaemic stroke compared with placebo.

### Study design

MASTER is a single-centre, patient and investigator-blinded, randomised, placebo-controlled, phase 2 clinical trial. It assigns patients with acute ischaemic stroke (within 7 days of onset) and motor impairment to either maraviroc (2×300 mg/day) or placebo for 90 days. The trial will randomise at a 1:1 ratio, powered to assess the superiority of maraviroc over placebo. The trial will be conducted at the Stroke Centre of the Geneva University Hospital, Switzerland.

### Recruitment

All patients admitted to the Stroke Centre will be screened during the daily clinical rounds conducted by board-certified stroke neurologists to ensure unbiased recruitment. Eligible patients will be enrolled within 7 days of onset.

### Eligibility criteria

The inclusion and exclusion criteria for the MASTER trial are shown in box 1.

Box 1Inclusion and exclusion criteria of efficacy and safety of the MASTER trialInclusion criteriaInformed consent by signature.Older than 18 years old.Acute ischaemic stroke (stroke onset within 7 days of randomisation).Contralateral, unilateral, incomplete upper limb paresis.Unilateral motor impairment with a Fugl-Meyer Upper-Extremity Score of less than 63/66.Residual voluntary finger extension of at least 10°.Exclusion criteriaPregnancy or lactation or positive pregnancy test in women of childbearing age (due to contraindication of maraviroc).Prestroke handicap with modified Rankin Scale >2.Diseases affecting motor function (eg, Parkinson’s disease, amyotrophic lateral sclerosis, amputation).Participation in another study with an investigational medicinal product within 30 days of randomisation.Enrolment of the investigator, his/her family members, employees and other dependent persons.Known hypersensitivity or allergy to maraviroc, peanuts, soy and/or mannitol.History of significant liver disease, hepatitis, elevated liver function tests (greater than 1.5 times the upper limit of normal).History of significant renal disease or end stage renal disease/dialysis, acute renal injury, creatinine clearance of less than 30 mL/min/1.73 m^2^.Patients with cardiovascular comorbidities and risk for orthostatic hypotension (eg, symptomatic heart failure, active coronary disease).HIV infection.Concomitant use of strong CYP3A4 inhibitors.Concomitant use of strong CYP3A4 inducers.MASTER, Maraviroc for Stroke Recovery.

### Blinding and randomisation

Trial participants, care providers, outcome assessors, investigators and the study team will be blinded to treatment allocation throughout the trial. Blinding is maintained by the pharmacy of the Clinical Trial Unit (CTU), which prepares identical capsules containing either maraviroc 150 mg or placebo, indistinguishable in appearance and packaging. Each treatment bottle is labelled with a unique randomisation number. All trial data are managed through the SecuTrial clinical database, which is fully blinded to treatment assignment. Study unblinding will occur only after database lock and validation of the final statistical analysis plan by the investigators and sponsor. Unblinding of an individual participant’s allocation is only permitted in the event of a serious adverse event (SAE), when knowledge of the treatment arm is essential for clinical decision-making.

Randomisation (1:1) will be conducted by an independent statistician from the CTU at the Geneva University Hospital. A computer-generated list will be created using random permuted blocks of variable sizes (2, 4 and 6) to ensure allocation concealment. Stratification will be performed by:

Side of infarct (left vs right hemisphere)Degree of finger extension (Fugl-Meyer Extension Subscore: 1 or 2 points)

This results in four randomisation strata, ensuring balance across treatment arms with respect to the laterality and severity of motor impairment.

### Intervention

The experimental intervention will be the administration of Maraviroc. The dosage will be 300 mg two times per day orally (2 capsules of 150 mg in the morning and 2 capsules of 150 mg in the evening). The experimental product will be reconditioned by the HUG pharmacy (crushed, mixed with mannitol and prepared in a capsule) from the original product to match the placebo. Placebo will be mannitol in identical capsules.

All patients will be treated with standard of care including secondary stroke prevention strategies in line with institutional and European guidelines (European Stroke Organisation guidelines on secondary stroke prevention^8^). All participants will receive standard neurorehabilitation according to our institutional stroke rehabilitation programme, aligned with European Stroke Organisation guidelines,^9^ which is currently recommended to include a minimum of 20 hours of intensive repetitive arm training 3–5 times per week over 4–6 weeks. During inpatient rehabilitation, detailed information on therapy content and focus (including upper-limb-specific and task-oriented training) will be recorded. During outpatient rehabilitation, rehabilitation exposure will be quantified by weekly therapy hours. This will enable controlling both for the number of hours of therapy received and percentage of patients meeting ESO guideline requirements, based on the reported therapy content.

### Criteria for discontinuing or modifying allocated interventions

There will be no dose modifications in this study, as patients whose dose should be reduced (presenting with estimated glomerular filtration rate (eGFR) <80 mL/min or prescribed concomitant strong CYP3A4 inhibitors) are excluded by design. Allocated intervention will be discontinued in the following situations:

Pregnancy.Liver toxicity: liver function tests (LFTs) reach Common Terminology Criteria for Adverse Events (CTCAE) grade ≥3 with bilirubin ≥1.5× the upper limit of normal and normal alkaline phosphatase, or LFTs reach grade ≥3 alone.Renal impairment: eGFR<30 mL/min.Cardiovascular: significant symptoms or findings of heart failure (eg, severe hypotension, arrhythmia) as assessed through ECG, vitals and clinical evaluation, treatment may be stopped based on clinical judgement.Infections or hypersensitivity: serious infection, significant eosinophilia or hypersensitivity reactions.Other safety concerns: Any emerging AE deemed to pose undue risk to the participant will lead to discontinuation, as determined by the investigator.

All safety-related discontinuations will be documented and reviewed by the study team.

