### Relevant concomitant care permitted or prohibited during the trial

The use of strong CYP3A4 inhibitors or inducers is prohibited and constitutes an exclusion criterion. All other pharmacological treatments are permitted and will be recorded. Non-pharmacological supportive therapies, such as physiotherapy, occupational therapy and speech therapy, are allowed and encouraged as part of standard post-stroke care and will continue throughout the study.

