### Safety outcomes

CTCAE v5.0-defined AEs through 180 days, including major adverse cardiovascular events (ie, acute myocardial infarction, acute coronary syndrome, stroke, heart failure, cardiovascular and all-cause mortality, revascularisation), liver-related AEs and infectious complications. SAEs will be tracked continuously through 180 days post randomisation.

Blood samples will be collected at each visit for safety monitoring. Participants of childbearing potential will undergo a urine pregnancy test at each visit. Samples will be processed and stored under standardised conditions.

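### The no-dose-modification rule assumes that patients with eGFR below 80 mL/min are excluded, but the eligibility box sets its only numeric renal limit at 30

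*Protocol article*

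**What the plan says.** Four sections of the protocol article bear on this point.

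- **Criteria for discontinuing or modifying allocated interventions.** The rule is "There will be no dose modifications in this study". The reason given is that patients whose "dose should be reduced (presenting with estimated glomerular filtration rate (eGFR) <80 mL/min or prescribed concomitant strong CYP3A4 inhibitors) are excluded by design". Among the stopping criteria, the renal one is "Renal impairment: eGFR<30 mL/min".
- **Eligibility criteria (Box 1).** The box is presented as the trial's inclusion and exclusion criteria. Its renal exclusion is "History of significant renal disease or end stage renal disease/dialysis, acute renal injury, creatinine clearance of less than 30 mL/min/1.73" m².
- **Intervention.** "The dosage will be 300 mg two times per day orally", with no variation by renal function.
- **Relevant concomitant care permitted or prohibited during the trial.** "The use of strong CYP3A4 inhibitors or inducers is prohibited and constitutes an exclusion criterion". This agrees with Box 1, so the drug-interaction half of the rationale is sound.

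No section states an exclusion for eGFR below 80 mL/min other than the sentence that asserts it is already in place.

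**The concern.** The sentence ruling out dose changes describes the eligibility criteria, so it can be checked against them. It names two groups who would need a lower dose and says that neither can enter. One group is indeed kept out. The other is kept out only in part: Box 1 applies its numeric limit at 30, not at 80.

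What is at stake is dosing safety. Staff who screen from Box 1 would accept patients whom another section says should have a reduced dose, and no reduction is available once they are randomised. Treating staff and investigators are blinded, so protection depends on the entry and stopping rules being right. Those rules currently carry two different numbers.

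**Working it through.** The check is mainly a comparison of text. The plan has no figure to reproduce on this point, and the sample size of 80 does not depend on it.

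**Step 1: the thresholds side by side**

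| Place in the protocol article | Measure | Limit | Effect |
|---|---|---|---|
| Criteria for discontinuing or modifying, rationale | eGFR, mL/min | below 80 | said to be excluded at entry |
| Eligibility criteria, Box 1 | creatinine clearance, mL/min/1.73 m² | below 30 | excluded at entry |
| Criteria for discontinuing or modifying, stopping rule | eGFR, mL/min | below 30 | treatment stopped |

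Gap between the two entry limits: 80 − 30 = 50 units. The unreconciled band is 30 to <80.

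**Step 2: could the units explain it?**

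Box 1 indexes to 1.73 m² and the rationale does not. The conversion is:

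unindexed value = indexed value × BSA / 1.73

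The documents give no body surface area (BSA), so the values below are assumed.

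- BSA 1.4 m²: 30 × 1.4 / 1.73 = 24.3 mL/min
- BSA 2.0 m²: 30 × 2.0 / 1.73 = 34.7 mL/min
- BSA 2.4 m²: 30 × 2.4 / 1.73 = 41.6 mL/min

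For the two limits to coincide, BSA would have to be 80 × 1.73 / 30 = 4.61 m², which is not plausible. Creatinine clearance and eGFR are also different measures, but that difference does not turn 30 into 80.

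**Step 3: could the non-numeric renal terms cover the band?**

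Significant renal disease is not defined in the article. It cannot mean everything below 80, because the same criterion sets its own number at 30, and that number would then do nothing. The term and the acute-injury exclusion will remove some patients in the band. A patient with moderately reduced function and no such history still passes.

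**Step 4: could the rationale mean low eGFR only in combination with an inhibitor?**

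No. The two conditions are joined by *or*, so low eGFR alone is given as a reason to reduce the dose.

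**Step 5: what happens to a patient in the band?**

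Take a patient at 50 mL/min with none of the other renal exclusions. Box 1 does not exclude this patient. Allocation is 1:1. On maraviroc the dose is 300 mg twice daily for 90 days, with no reduction permitted. The numeric stopping rule acts only below 30.

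**Step 6: number affected**

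This cannot be computed. The article gives no distribution of renal function for the target population.

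**The case against.** The textual mismatch is hard to dispute. The case on the other side concerns how much follows from it.

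- **It may be only a reporting slip.** The article condenses a full protocol reviewed by an ethics committee and the Swiss regulator. If that protocol excludes eGFR below 80, Box 1 is misprinted and nobody is misdosed. This stands as a limit on what can be claimed: the conflict is certain, actual misdosing is not. It does not remove the need to correct the article, and it is why the fix starts with the full protocol.
- **The 50-unit gap does not count patients.** This is correct. The other renal exclusions shrink the exposed group by an unknown amount, but they do not empty it.
- **Falls below 80 during treatment are a separate matter.** The rationale concerns patients who present with low eGFR, so it reads as status at entry, and a stopping limit below the entry limit is not in itself a contradiction. The article also provides that "Blood samples will be collected at each visit for safety monitoring" and requires discontinuation for any emerging adverse event that the investigator judges to pose undue risk. This largely stands. The on-treatment point is secondary, and the conclusion does not rest on it.
- **A dose rule does exist between 30 and 80: the full fixed dose.** This is fair. If Box 1 is right, what is missing is a valid justification for that dose, because the one offered is untrue. A renal dose reduction is one remedy and not the only one.
- **The primary outcome, randomisation and primary analysis are untouched.** This is true. The issue is safety and eligibility.

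**Conclusion.** The concern holds. As written, the renal half of the reason for having no dose modifications is false: the article says patients below 80 mL/min cannot enter, while its eligibility criteria exclude numerically only below 30. Patients from 30 to <80 without Box 1's other renal conditions are eligible and, if allocated to maraviroc, receive a dose that the article itself says should be reduced.

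The thresholds differ by 50 units, and no plausible body size reconciles them. That check rests on an assumed surface area of 1.4 to 2.4 m². The number of patients affected is unknown, and only those in the maraviroc arm would receive the unreduced drug dose. The document does not show which threshold is the error.

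This is an error in a stated safety threshold, not a detail left to another document. Recruitment opened on 14 July 2025, so it must be corrected.

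**What to change.** 1. **Establish which limit the full approved protocol uses.** If it is consistent, only the article needs correcting.
2. **Use one renal measure and one threshold** in the eligibility box, the dose-modification rationale and the stopping rule, by one of two routes:
   - *80 is intended:* change the Box 1 exclusion to eGFR below 80 mL/min, and say what happens if a participant falls below 80 during the 90 days.
   - *30 is intended:* correct the rationale sentence, and state and justify the dose for 30 to <80 mL/min. If that dose is lower, apply the reduction by capsule count in both arms. Each dose is two 150 mg capsules, so this keeps the blind. If the full dose is kept, give the reason.
3. **Check the baseline renal function of every participant already randomised** against the confirmed rule.

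The cost is one document check, a correction (or an amendment if the full protocol has the same conflict), and one review of renal results already on file. An exclusion at 80 may slow recruitment at this single centre. The sample size and primary analysis need no change.

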### Relevant concomitant care permitted or prohibited during the trial

The use of strong CYP3A4 inhibitors or inducers is prohibited and constitutes an exclusion criterion. All other pharmacological treatments are permitted and will be recorded. Non-pharmacological supportive therapies, such as physiotherapy, occupational therapy and speech therapy, are allowed and encouraged as part of standard post-stroke care and will continue throughout the study.

### Strategies to improve adherence to interventions

Participants will receive clear verbal and written instructions regarding the study intervention schedule. Study medication will be dispensed at designated visits, and participants will be asked to return all unused tablets and packaging at subsequent visits (visits 3, 4 and 5). Adherence will be assessed by tablet counts and direct questioning. Tablets not returned will be assumed to have been taken.

Phone follow-up calls will be conducted between visits (weeks 2, 6 and 10) to monitor adherence, reinforce compliance and identify potential AEs. Compliance will be defined as taking 80%–120% of the prescribed doses. Non-compliance will be documented and reviewed. A full dispensing log will track all medication dispensed, returned and destroyed.

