### Data collection and management

All outcomes will be assessed using standardised procedures by trained personnel. Data will be collected at baseline and at 30, 60, 90 and 180 days poststroke. Participants who discontinue the intervention will be encouraged to complete all assessments. When in-person visits are not feasible, alternative follow-up (eg, home or phone visits) may be arranged. The patient timeline is shown in figure 1.

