### Statistical methods for primary and secondary outcomes

Two analysis sets will be used: an intention-to-treat population (all randomised participants who received ≥1 dose, analysed per allocation) and a per-protocol population (excluding those with major protocol deviations, eg, <80% medication adherence). Missing data will not be imputed.

The primary outcome (FMA-UE) will be compared between groups using a t-test or non-parametric equivalent. An adjusted analysis using multivariate linear regression will account for stratification variables (infarct side, finger extension ability) as well as other variables like CCR5-Δ32 loss-of-function mutation carrier status to account for confounding effects on motor recovery and treatment response. Secondary outcomes will be analysed via regression models adjusted for the same covariates. Linear mixed models will include time point and group as fixed effects and participant ID as a random effect to account for repeated measures. To assess whether maraviroc promotes recovery via peri-infarct plasticity, causal mediation analysis will estimate direct and indirect effects (via changes in connectivity/metabolism from baseline to 90 days). The analysis includes three regression steps, with the indirect effect tested via the Sobel method. Weekly rehabilitation hours (during the first 90 days) will be included as a covariate. A similar approach will be applied to motor learning outcomes. Safety analyses will summarise the number and proportion of participants with ≥1 SAE, AE of special interest, or death by day 90 in each group.

Analyses will be conducted in R, MATLAB or Python using appropriate packages. Imaging data will be processed with FSL, FreeSurfer, SPM and DSI Studio, depending on modality.

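### Counting every unreturned capsule as taken can only overstate adherence, so participants who under-took the drug can stay in the per-protocol set; separately, the visit clock and the 90-day course need reconciling

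*Protocol article*

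**What the plan says.** Under Strategies to improve adherence to interventions, participants are "asked to return all unused tablets and packaging at subsequent visits (visits 3, 4 and 5"), and the section states: "Adherence will be assessed by tablet counts and direct questioning". It then gives the rule at issue, "Tablets not returned will be assumed to have been taken", and a definition: "Compliance will be defined as taking 80%–120% of the prescribed doses". The same section provides for phone calls at weeks 2, 6 and 10, review of documented non-compliance, and a dispensing log.

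Under Statistical methods for primary and secondary outcomes, the second analysis set is "a per-protocol population (excluding those with major protocol deviations, eg, <80% medication adherence").

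On timing, Study design assigns participants "to either maraviroc (2×300 mg/day) or placebo for 90 days". Data collection and management says: "Data will be collected at baseline and at 30, 60, 90 and 180 days poststroke". The primary outcome is also titled by days from stroke, and the Figure 1 caption makes visit 5 (V5) its time point. Randomisation may come up to 7 days after onset. Safety outcomes, by contrast, follows serious adverse events to 180 days counted from randomisation.

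**The concern.** A per-protocol set is useful only if membership reflects drug actually taken. Under the stated rule, membership depends partly on whether leftovers come back. Of two participants with the same low intake, the one who returns the bottles can be excluded and the one who loses or keeps them can be retained. That behaviour occurs after randomisation and need have nothing to do with exposure.

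The situation is realistic. Data collection and management encourages participants who discontinue to complete assessments, and it allows phone visits when attendance is not feasible. Nothing can be handed back by phone, so the default then credits full intake.

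The per-protocol analysis is the only one in the article defined by adherence. Retaining unrecognised non-takers would pull its estimate towards no effect.

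The timing question touches the same count. The last listed return is V5. If V5 is fixed from stroke while treatment runs 90 days from a later first dose, either the course is shorter than 90 days or it continues past the last count and the primary assessment. The article does not say which.

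**Working it through.** **The plan's own figure.** The article gives no derived adherence figure. Its one derived number, the sample size, reproduces: 2 × (1.960 + 0.842)² × 17.5² / 12.4² = 31.3, so 32 per arm (two-sided 5% assumed), 64 in total, and 64 / 0.80 = 80. The present point does not rest on it.

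**Inputs.** Four capsules a day (Intervention) for 90 days (Study design) gives 4 × 90 = 360. The 80% cut-off is 0.80 × 360 = 288. I read tablets in the adherence section as these capsules.

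**Step 1: effect of the unreturned-drug rule.** Let t be true adherence and U the number of unreturned leftover capsules. Leftovers are 360 × (1 − t). Counted adherence is 1 − returned/360 = t + U/360. Since U cannot be negative, counted adherence is never below t. It reaches 80% when U = 288 − 360t.

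| True adherence | Leftover capsules | Unreturned needed to read 80% | Share of leftovers |
|---|---|---|---|
| 75% | 90 | 18 | 20% |
| 70% | 108 | 36 | 33% |
| 50% | 180 | 108 | 60% |
| 0% | 360 | 288 | 80% |

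On the count alone, a participant who returns nothing reads 100% whatever was taken.

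**Step 2: effect of the visit clock.** Let d be days from stroke to first dose. Randomisation can be on day 7. The Figure 1 caption places the V2 assessments within 24 hours of starting medication, so d could reach about 8. Capsules due by day 90 from stroke are 4 × (90 − d).

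| d | Treatment days by V5 | Capsules due | Full adherer against 360 | True adherence needed to read 80% of 360 |
|---|---|---|---|---|
| 0 | 90 | 360 | 100% | 80% |
| 7 | 83 | 332 | 332/360 = 92.2% | 288/332 = 86.7% |
| 8 | 82 | 328 | 328/360 = 91.1% | 288/328 = 87.8% |

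A full adherer never falls below 80% through timing. With a fixed denominator of 360, only late starters with true adherence between 80% and about 87–88% would be wrongly excluded. With capsules due to date as the denominator, there is no shortfall.

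Capsules kept at V5 to finish a 90-day course are unreturned, so the rule counts them as taken: 360/332 = 108% or 360/328 = 110% of doses due, still inside the 80–120% range.

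**Step 3: illustration of dilution, under assumption.** Take the planned 32 evaluable per arm, suppose hidden non-takers on maraviroc gain nothing, and suppose all others gain the planned 12.4 points. One such participant gives 12.4 × 31/32 = 12.0; four give 12.4 × 28/32 = 10.9. The true number is unknown.

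**The case against.** The strongest reply is that the count does not stand alone. The article also provides direct questioning, calls at weeks 2, 6 and 10 and a dispensing log, and it requires safety-related discontinuations to be documented and reviewed. A reader might infer that someone who stops at day 30 and returns nothing (30 × 4 / 360 = 33% intake) is bound to be scored 100%. The documents do not support that. An open stop could be picked up by these sources, and the list of major deviations is open-ended, so a known early stop could be excluded on that ground. This stands: misclassification is a risk, not a certainty. It does not remove the point, because the only stated rule for missing capsules is that they were taken, and nothing says that another source overrides it.

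A second tempting reading is that the per-protocol threshold becomes 87%. That needs both a start on day 7 and a denominator fixed at 360, and the article does not fix the denominator. Nor are capsules still due at V5 simply scored as untaken: if kept, they count as taken. The two mechanisms therefore pull in opposite directions.

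A third is that the 80–120% compliance range contradicts the under-80% exclusion. It does not. The exclusion is offered as an example, and the article does not say that intake above 120% is retained.

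Finally, the full protocol or analysis plan may settle the denominator and the order of precedence between sources. That is fair, and their absence here is no fault. The finding rests on an assumption that the article states and on time origins that do not line up.

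**Conclusion.** The point holds in limited form. The stated assumption biases counted adherence upwards only, and it feeds an 80% cut-off that defines the per-protocol set. Modest losses are enough near the cut-off (18 capsules at 75% true intake, 36 at 70%); larger ones are needed further from it (108 at 50%). These figures assume a full 360-capsule course and that questioning and calls either miss the non-adherence or do not override the count. Neither the intention-to-treat analysis nor the sample size is affected.

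The timing inconsistency is separate. Read literally, V5 precedes the end of a 90-day course for anyone starting after the day of stroke, by up to about 7 to 8 days; for a start on the day of stroke the gap is zero. If V5 were in practice counted from randomisation, as serious adverse event follow-up is, the gap would shrink to about 1 day at most. Timing alone would not take a full adherer below 80%.

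**What to change.** 1. Replace the assumption: unreturned capsules are recorded as unknown.
2. State that direct questioning, the week 2, 6 and 10 calls and documented discontinuations override the capsule count where they disagree.
3. Use capsules due from first dose to the count date as the denominator.
4. Run the per-protocol analysis with and without participants whose intake cannot be verified. Blanket exclusion is debatable: it also selects on behaviour after randomisation, and it would drop true adherers who merely discarded their packaging. It therefore belongs in a sensitivity analysis.
5. Reconcile the sections that time visits and the primary outcome from stroke, set treatment at 90 days, and follow serious adverse events from randomisation. Which should give way is for the trial team to decide.

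Items 1 to 4 change wording and use data the trial already plans to collect. The cost is slightly more analysis work and a possibly smaller set in the sensitivity analysis. The article has the final analysis plan validated before unblinding, so these changes can still be made blind.
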